**2. INTRODUCTION AND RATIONALE**

*2.1 Introduction / background*

The incidence of metachronous metastases after curative colon and rectum resections is approximately 30-50%, with an increasing incidence dependent on the initial stage. Predominant sites of first recurrence in the population with recurrent disease are the liver (± 40%), lung (± 30%) and local recurrence (± 25%) (Kobayashi). These types of recurrent disease can be eligible for curative resection, which is now feasible in an estimated 10-30%. The increase in survival after metastasectomy for resectable recurrent disease is high, with a 5 year overall survival after metastasectomy of approximately 30% for all three types of recurrent disease (Goldberg, Bentrem, Pfannschmidt). It is predominantly dependent on achievement of a R0 resection and the number of metastases, the last probably corresponding to tumor behaviour.

*2.2. Follow-up*

After curative treatment of colorectal cancer, patient surveillance is recommended to detect curable recurrent disease or new primary tumors in an early phase. There was a statistically significant increase in feasibility of intended curative resection of recurrent disease in 5 prospective randomised studies and in the 5 year overall survival in 4 of the 5 studies. Based on the literature, both the Dutch guideline (CBO 2008), the Canadian guideline and the US guideline (ASCO 2005) propose a high intensity program of regular office visits, imaging studies (CBO: liver ultrasound, Canada: liver imaging, ASCO: Computed Tomography (CT) chest-abdomen) and CarcinoEmbryonicAntigen (CEA) tests. Imaging is advised since not all recurrences are detected with an early CEA raise. The value of physical examination in detecting recurrent disease is low (Borie, Sugarbaker).

*2.3. Carcinoembryonic antigen (CEA)*

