## *6.4. Sample size calculation*

Given current usual care with pre-operative staging with CT of the thorax and abdomen and neo-adjuvant therapies, the expected occurrence of metachronous metastases is approximately 25%. Of these, the expected percentage of resected metastases in patients is 10% in the control group and 25% in the intervention group. Given a significance level of 5% and a power of 80%, 115 patients with metastases in both groups are needed. Given an expected recurrence rate of 25%, 460 patients per group are needed.

Because in this study the moment to start the intervention instead of patients will be randomized, we calculated a correction factor C. Assuming a standard deviation in the effect of hospitals on the outcome of 0.1, C has a value of 1.71. (van Houwelingen) Therefore about 800 patients per group are needed.

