### *8.1.2. Secondary study parameters/endpoints*

Calculation of the optimal threshold values and measurement frequency of CEA by

means of calculating ROC curves based on actually measured CEA values.

Percentage of patients that show metastasis on CT thorax/abdomen when the rise of CEA at the chosen threshold values is above normal, and percentage of patients that do not show metastasis on CT thorax/abdomen despite rise of CEA.

Percentage of patients that show metastasis on regular CT Thorax/abdomen with no rise of CEA above normal (false negative rate of CEA measurement)

Overall survival, disease-free survival and recurrence-free survival

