## *Study procedures*

## Vena puncture bi-monthly: measurement serum CEA and serum ‘in storage’

## Vena punctures are carried out at local laboratories.

## CT scan abdomen/thorax

## At year 1 (abdomen) and 2 (thorax/abdomen)

## If CEA rises as outlined in the flowchart, a CT scan thorax/abdomen will be performed because of the suspicion for local recurrence or metastatic disease. If this scan is made coincidently at or around year 1, 2 or 3, the standard scan will be cancelled.

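### Section 8.1.2 scores CTs after a CEA rise, and the CEA false negative rate, on metastasis alone, so isolated local recurrence is not counted as recurrence in either

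*Protocol*

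**What the plan says.** Section 8.1.2 fixes three percentages that link CEA to CT. Two concern patients with a CEA rise: those whose CT shows metastasis, and the "percentage of patients that do not show metastasis on CT thorax/abdomen despite rise of CEA". The third is the percentage of patients who "show metastasis on regular CT Thorax/abdomen with no rise of CEA above normal (false negative rate of CEA measurement"). All three are worded on metastasis. Neither 8.1.2, nor the other parameters in 8.1.3, nor the secondary endpoints in 4.2 have a class for local recurrence by CEA status.

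Elsewhere the target is wider:

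- The study procedures in section 8 say that after a CEA rise "a CT scan thorax/abdomen will be performed because of the suspicion for local recurrence or metastatic disease".
- Section 2.2 gives the purpose of follow-up: "patient surveillance is recommended to detect curable recurrent disease or new primary tumors in an early phase". It justifies imaging in the same terms: "Imaging is advised since not all recurrences are detected with an early CEA raise".
- Section 2.1 names liver (about 40%), lung (about 30%) and local recurrence (about 25%) as the main first sites, and adds: "These types of recurrent disease can be eligible for curative resection".

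**The concern.** The triggered CT is ordered for two conditions and scored on one. In section 2.2 a CEA miss is a missed recurrence; in 8.1.2 it is a missed metastasis. Under the literal rule, a local recurrence that CEA signals earns the test no credit, and one that CEA fails to signal is not held against it.

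Section 3 aims at a guideline on CEA and CT for routine follow-up. A reader of that guideline will want to know how often a CEA rise leads to a recurrence and how often a recurrence shows up without a rise. The percentages as defined answer both questions for metastases only, and a reader could easily take the no-metastasis class for false alarms. What is at stake is the usefulness of these secondary measures.

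**Working it through.** **The plan's own group size.** Section 6.4 needs 115 patients with metastases per group and says: "Given an expected recurrence rate of 25%, 460 patients per group are needed". Check: 115 / 0.25 = 460. With the correction factor, 460 × 1.71 = 787, stated as about 800. The protocol gives no figure for the point at issue, so what follows is an identity and a ceiling.

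**Classes under the literal rule.**

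| Finding | CEA rise, triggered CT | No CEA rise, scheduled CT |
|---|---|---|
| Metastasis | shows metastasis | false negative |
| Local recurrence only | no metastasis | not counted |
| No recurrence | no metastasis | not counted |

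The middle row is treated exactly like the bottom row.

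**Triggered CTs.** Let L be the share of triggered CTs that show local recurrence only. Then:

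no-metastasis % = no-recurrence % + L

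The gap is exactly L percentage points. The protocol does not give L.

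**Ceiling on the patients concerned, intervention group.** Inputs: 800 patients and a 25% rate (6.4); a 25% local share of first recurrences (2.1), taken as the maximum for isolated local recurrence; 10% as an assumed lower value. The site shares add up to 40 + 30 + 25 = 95%, which suggests little overlap, but the protocol does not say whether patients with local recurrence also had distant disease.

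- Planned events: 800 × 0.25 = 200.
- If the 25% rate means recurrence at any site: 200 × 0.25 = 50, or 200 × 0.10 = 20.
- If it means metastases only, local recurrences come on top: (200 / 0.75) × 0.25 = 66.7, or (200 / 0.90) × 0.10 = 22.2.

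This gives 20 to 67. Only local recurrences seen on a triggered or scheduled CT enter the three percentages, so each count is an upper limit for its assumed share.

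**False negative rate.** Suppose it is read as the share of patients with disease whom CEA missed. Let s_M and s_L be the sensitivity of CEA for metastasis and for isolated local recurrence, and w the share of all recurrences that are local only. Then:

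rate on any recurrence = (1 − s_M) + w × (s_M − s_L)

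If s_L = s_M, the rate does not change. It moves only if sensitivity differs by site, and the protocol gives neither value. If the rate is instead taken over all patients with a scheduled CT and no rise, it goes up by the share of those CTs that show local recurrence only, which is also not given. No size can be stated on either reading.

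**The case against.** The strongest reply is that nothing here is inconsistent. Secondary endpoint 3 in section 4.2 asks whether CT can localise the metastasis when CEA suggests metastatic disease, and the CT percentages answer that question. The primary endpoint is also about liver and lung metastases. This stands. A reader might infer that 8.1.2 contradicts the endpoints; it does not, and the metastasis figures should be kept.

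Second, the protocol uses the terms loosely. Section 6.4 applies 25% to both metastases and recurrence, and section 2.1 speaks of metastasectomy for all three types of recurrent disease. A broad meaning of metastasis is therefore possible. But the study procedures name local recurrence beside metastatic disease as something separate, and no definition widens the term. If the broad meaning was intended, one line in 8.1.2 would settle it.

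Third, 8.1.2 does not call the no-metastasis class false positive, and that class is literally true of an isolated local recurrence. This stands too. The label on the false negative rate is the weaker spot, although its definition sits beside it.

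Fourth, recurrence-free survival is also listed in 8.1.2 and needs recurrence to be recorded, so an any-site table could be added at the analysis stage. That shows the fix is cheap. It does not remove the point, because the protocol itself states the narrower scoring rule.

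Two further readings are not supported. The ROC sentence in 8.1.2 names no reference outcome, so it cannot be called metastasis-only. The branch in 7.2.1 for CTs without liver or lung metastases ends in interdisciplinary discussion, and the flowchart in addendum 2 is not at hand, so no gap in care can be inferred.

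**Conclusion.** The point holds as a low-cost improvement to secondary measures. On the literal wording, isolated local recurrence falls into the no-metastasis class after a CEA rise and is left out of the false negative rate on scheduled CT, although the protocol names it as a target of the triggered CT and as potentially curable.

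The certain effect is the identity: the no-metastasis percentage overstates the no-recurrence percentage by L points, with L unknown. The range of 20 to 67 patients is a ceiling. It rests on 800 patients in the intervention group, the 25% rate, a local share between an assumed 10% and the protocol's 25%, and the assumption that every such recurrence is isolated and found on a relevant CT.

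A reader might infer that the false negative rate is biased by a known amount, or that the main result is at risk. Neither follows: the direction and size of any change in the miss proportion depend on sensitivities that the protocol does not give, and the primary endpoint, sample size and error rates do not use these parameters.

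**What to change.** In section 8.1.2, replace the three CEA/CT percentages with:

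- among patients with a CT triggered by a CEA rise, the percentage with recurrence at any site (local, liver, lung, other) and the percentage with no recurrence at any site;
- the percentage with recurrence at any site on a scheduled CT without a CEA rise, as the false negative rate;
- each of these also for metastases alone, as the subset that answers secondary endpoint 3.

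The cost is a change of wording and slightly more reporting. No extra patients, visits or procedures are needed. The ROC sentence and section 7.2.1 need no change on this account.

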*7.2.1.Procedure when CEA crosses the threshold value (see flowchart, addendum 2)*

Increase > 20% in 8 weeks > repetition of CEA measurement in 4 weeks, also measuring CRP level.

Increase in second measurement after 4 weeks > 10%, with a lower static threshold value of 2.5 ng/ml > outpatient clinic visit; if explanation of rise is clear from clinical reasons (ie., active infection): treat infection and re-assess CEA value after 4 weeks. If increase:

-> Evaluation by helical CT Thorax/abdomen within two weeks:

-> Outpatient clinic within 7 days after CT scan

At this visit an assessment is made evaluating

- The presence of resectable metastasis in liver or lung

- Physical signs suggesting other localizations of recurrent disease

- Fitness of the patient to undergo treatment of metastasis

When curable metastases are found and the patient can undergo metastasectomy

-> Treatment at own or referral centre according to the current standard

When irresectable metastases are found or the patient is unfit to undergo metastasectomy

-> Referral to medical oncology for palliative chemotherapy according to the current standard;

-> Referral to radiotherapy when palliative radiation is clinically considered

When no liver and lung metastases are found on CT scan

-> CEA measurement as before

-> Next step dependent on outcome, to discuss in interdisciplinary platform

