2. Only when the patient is fit enough for metastasectomy, follow-up is started. This is assessed at the first outpatient visit and if necessary delayed at the surgeon’s judgment. [↑](#footnote-ref-3)
3. When a patient underwent a CT thorax/abdomen due to a rise in CEA during follow-up, the study CT at year 1 and 2 will not be made. [↑](#footnote-ref-4)
4. When a full colonoscopy has been performed pre-operatively, the colonoscopy at year 1 is not indicated. [↑](#footnote-ref-5)

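### The protocol's 'false negative rate of CEA' is restricted to regular CT, so it is not missed recurrences over all recurrences

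*Protocol*

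**What the plan says.** Section 8.1.2 of the protocol defines and names the parameter: "Percentage of patients that show metastasis on regular CT Thorax/abdomen with no rise of CEA above normal (false negative rate of CEA measurement". It gives no denominator. Metastases found after a CEA rise appear in a separate item of the same section: "Percentage of patients that show metastasis on CT thorax/abdomen when the rise of CEA at the chosen threshold values is above normal". Nothing says that the two items are combined.

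Three other places determine who has a regular CT in the intervention period:

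- Section 7.2.1 sends a patient whose CEA rise is confirmed, and who meets the other steps there, to a separate scan: "Evaluation by helical CT Thorax/abdomen within two weeks".
- Footnote 3 says that after a CT "due to a rise in CEA during follow-up, the study CT at year 1 and 2 will not be made".
- The study procedures section is narrower about the triggered scan: "If this scan is made coincidently at or around year 1, 2 or 3, the standard scan will be cancelled".

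On coverage, the study procedures section lists the regular scans as "At year 1 (abdomen) and 2 (thorax/abdomen"), so the year-1 scan does not image the chest. Section 7.2 agrees on this and adds a thorax/abdomen CT at year 3.

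**The concern.** A false negative rate is FN/(FN + TP), where FN are recurrences without a CEA rise and TP are recurrences with one. The named quantity counts only what a regular CT shows, and the CEA pathway takes TP patients out of the regular-CT group. What remains is a different quantity, and its value depends on a denominator that the text does not give.

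Recurrences with normal CEA that come to light between scans, through symptoms, at colonoscopy, or in the chest around the abdomen-only year-1 CT are not counted at all, although each is a miss by CEA.

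Section 2.2 justifies imaging on the ground that CEA does not give early warning of every recurrence, and section 4.2 makes the relation between CEA and CT a secondary endpoint. A published false negative rate would be read as the share of recurrences that CEA misses, and under the natural readings of the text it would be wrong.

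**Working it through.** The protocol gives no value for this parameter, so there is no figure to reproduce. The check is a 2×2 table.

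**Inputs**
- Recurrence rate 25% and about 800 patients per group (section 6.4), hence 200 recurrences and 600 patients without.
- CEA sensitivity: not given; assumed 60–80%.
- CEA specificity: not given; assumed near 1, and 0.9 as an alternative.
- k, the share of CEA-positive patients who still have a regular CT that counts: not given. Footnote 3 read strictly means k = 0 at years 1 and 2; the study procedures wording allows k > 0.

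**Reading A: over all patients with a regular CT.** With k = 0 this is FN/(FN + TN) = 1 − NPV.

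| Sensitivity | FN | True rate, FN/200 | Specificity near 1, FN/(FN + 600) | Specificity 0.9, FN/(FN + 540) |
|---|---|---|---|---|
| 60% | 80 | 40% | 80/680 = 11.8% | 80/620 = 12.9% |
| 70% | 60 | 30% | 60/660 = 9.1% | 60/600 = 10.0% |
| 80% | 40 | 20% | 40/640 = 6.3% | 40/580 = 6.9% |

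The true rate is 2.9 to 3.4 times the reported one. If CEA-positive patients keep their regular CT, the result does not improve: at sensitivity 70% and specificity 0.9 it falls from 10.0% at k = 0 to 60/800 = 7.5% at k = 1.

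*Dependence on the recurrence rate.* Section 2.1 cites 30–50%. At 50%, specificity near 1 and k = 0, sensitivity 60% gives 0.20/(0.20 + 0.50) = 28.6% against 40% (1.4 times), and sensitivity 80% gives 0.10/(0.10 + 0.50) = 16.7% against 20% (1.2 times). At k = 0, Reading A is too low whenever TN exceeds TP. At 25% recurrence this means 600 × specificity > 200 × sensitivity, which any specificity above one third satisfies.

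**Reading B: over patients with metastasis on regular CT.** This is FN/(FN + k·TP). At sensitivity 70% (FN 60, TP 140; true rate 30%):
- k = 0: 60/60 = 100%
- k = 0.10: 60/74 = 81%
- k = 0.25: 60/95 = 63%
- k = 0.50: 60/130 = 46%
- k = 1: 60/200 = 30%

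It is too high for every k below 1, and k = 1 requires that no regular CT is ever cancelled, which both cancellation rules exclude.

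**Reading C: regular-CT misses over all metastases from any CT.** The text does not state this reading. If, say, 20% of the 60 misses surface outside regular CT but are still counted among the 200 recurrences, the result is 48/200 = 24% against a true 30%.

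**The case against.** The best reply is that no denominator is written, so Reading C may be what was meant. The adjacent item collects metastases after a CEA rise, so most of the 2×2 table is available, and a statistical analysis plan could settle the rest. For a comparison of CEA with CT, the yield of regular CT when CEA is normal is also useful in itself; on this view only the bracketed name is wrong. Part of this stands: the yield is worth reporting, and Reading C comes near the right value. But the protocol attaches the name to a quantity confined to regular CT, and even Reading C leaves out CEA-negative recurrences found by other routes.

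A reader might also infer more than the documents support:

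- *That the figure must be close to 100%.* This is the extreme of Reading B and rests on footnote 3 alone. The study procedures section cancels fewer scans, footnote 3 does not mention year 3, and section 7.2.1 triggers a CT only after a confirmed second increase, so patients with an unconfirmed rise keep their regular scan.
- *That the understatement could be tenfold.* This needs a recurrence rate near 10%, which is not in the documents. The rates they give, 25% and 30–50%, lead to smaller factors.
- *That this figure decides whether CT is needed beside CEA.* The protocol contains no such decision rule.
- *That the ROC analysis has the same fault.* The protocol plans it by "means of calculating ROC curves based on actually measured CEA values" and does not say how recurrence status is assigned. That is detail for an analysis plan, and CEA-negative patients do have scheduled CTs. No overstatement of sensitivity can be shown from the text.

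**Conclusion.** The point holds as a mislabelled secondary parameter. Followed as written, section 8.1.2 does not give FN/(FN + TP). At 25% recurrence, Reading A reports about a third of the true rate. Reading B overstates the rate by an amount that depends on how many regular CTs are cancelled. The sizes rest on assumed sensitivity, specificity and k, none of which the protocol supplies. The upward direction of Reading B follows from the cancellation rules alone; the downward direction of Reading A holds at 25% recurrence for any plausible specificity, but the gap narrows as recurrence rises. The primary endpoint, the sample size and the main comparison between follow-up schedules are not affected.

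**What to change.** - Define the false negative rate of CEA as confirmed recurrences in intervention time without a preceding protocol-defined CEA rise, divided by all confirmed recurrences in intervention time by any detection route (triggered CT, regular CT, symptoms, colonoscopy). State a fixed look-back window for the CEA rise.
- Keep the yield of regular CT in patients with normal CEA, reported separately under the name 1 − NPV.
- Record the mode of detection for each recurrence. The primary endpoint does not require it and section 8.1.3 does not list it, so it is a small added data item.
- Reconcile footnote 3 with the study procedures section on when a regular CT is cancelled, since this determines who is in the regular-CT group.

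The cost is a change of endpoint wording, one extra data field and a little analysis work.

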**4. Endpoints**

*4.1. Primary endpoint*

The increased percentage of patients with intended curative metastasectomy of liver- and lung metastases from colorectal carcinoma in the intensified follow-up schedule.

*4.2. Secondary endpoints*

1) Overall survival, disease specific survival, disease free survival

2) Calculation of the optimal threshold values and measurement frequency of CEA

3) The correlation between CEA and helical CT abdomen/thorax: specifically whether the metastasis can be localized when CEA values suggest metastatic disease.

4) Evaluation of the effects of the follow-up protocol: psychological effects and logistic effectuation

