**7. TREATMENT PERIODS**

*7.1. Control period*:

Outpatient clinic at 3 months after end of treatment (surgery or adjuvant chemotherapy)

Assessment for fitness to undergo metastasectomy[[2]](#footnote-3)

Care as usual according to the Dutch guidelines ([www.oncoline.nl](http://www.oncoline.nl/)) and local amendment. The actual care as usual given may differ per hospital. Herefore, the standard care as usual per hospital will be described.

Filling out the questionnaire “SF-12 “ after 12 months

*7.2. Intervention period*:

Outpatient clinic at 3 months after end of treatment (surgery or adjuvant chemotherapy)

Assessment for fitness to undergo metastasectomy2

During year 1

CEA measurement every 8 weeksatlocal laboratory, report results by letter. The possibilities for blood sampling at a local laboratory are now examinated per hospital. The measurement will take place at the hospital itself, samples will be mailed to the laboratory.

If no special events occur, no additional out patient clinic visits

At year 1 helical CT-abdomen[[3]](#footnote-4) and colonoscopy[[4]](#footnote-5)

Filling out the questionnaire “SF-12 “ after 12 months

Filling out the questionnaire of intensified follow-up at 1 year

One year after surgery outpatient clinic visit

- Results from evaluation (CT) and evaluation long term surgical results

- Update assessment for fitness metastasectomy

During year 2

CEA measurement every 8 weeks atlocal laboratory, report results by letter

If no special events occur, no additional out patient clinic visits

At year 2 helical CT thorax/abdomen4

Two years after surgery outpatient clinic visit

Results from evaluation (CT) and evaluation long term surgical results

Update assessment for fitness metastasectomy

During year 3

CEA measurement every 12 weeks atlocal laboratory, report results by letter

If no special events occur, no additional out patient clinic visits

At year 3 helical CT thorax/abdomen

Three years after surgery outpatient clinic visit

Results from evaluation (CT) and evaluation long term surgical results

Update assessment for fitness metastasectomy

All patients will be informed about the laboratory results by letter or email. In case of positive results patients will be invited to undergo a CT scan followed by an outpatient clinic visit. All patients will have access to the surgeon’s outpatient clinic in case of questions or clinical complaints.

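### The false-negative rate of CEA in 8.1.2 presumes a routine CT of thorax and abdomen, but the year-1 routine CT images the abdomen only

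*Protocol*

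**What the plan says.** Section 8.1.2 lists, among the secondary parameters: "Percentage of patients that show metastasis on regular CT Thorax/abdomen with no rise of CEA above normal", which it labels the false-negative rate of CEA. The same section derives optimal CEA thresholds and measurement frequency from ROC curves, without naming the reference that decides who has metastases.

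The scans that supply this reference are described elsewhere:

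- Section 7.2, first year: "At year 1 helical CT-abdomen". Second year: "At year 2 helical CT thorax/abdomen". A thorax/abdomen CT is also listed at year 3.
- Study procedures (8.2 in the table of contents) agrees on the first two scans: "At year 1 (abdomen) and 2 (thorax/abdomen").
- Section 7.2.1, after a confirmed CEA rise: "Evaluation by helical CT Thorax/abdomen within two weeks".
- Study procedures and footnote 3: a CT made because of a CEA rise takes the place of the standard scan.

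The abdomen-only field at year 1 therefore appears in two places and is not a slip in one line. Section 2.1 puts the lung at about 30% of first recurrences.

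**The concern.** At year 1, how much of the body is imaged depends on the result of the test being evaluated. A patient whose CEA has risen has the chest scanned; a patient whose CEA has not risen does not. A lung metastasis with a CEA rise can be counted as a CEA success. One without a rise is largely out of view and cannot be counted as a miss. If CEA rises before the year-2 scan, that patient is recorded as detected by CEA.

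This is differential verification, and it pushes the false-negative rate down. The ROC curves share the problem so far as they take disease status in CEA-negative patients from the routine CT. Lung is one of the two metastatic sites in the main endpoint, and the objective is a follow-up guideline built on CEA and CT, so an optimistic miss rate for lung would matter to its users.

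**Working it through.** The protocol states no sensitivity or false-negative rate for CEA, so there is no figure to reproduce. The check has two parts, one for each way of reading 8.1.2. The denominator is not spelled out; I follow the label and use silent / (silent + CEA-flagged) among patients with metastases.

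**Inputs**
- Lung share L = 0.30 (section 2.1, all first recurrences in the lung).
- True miss rate m: not given; assumed 0.20, 0.40, 0.60.
- Share f of metastases judged at year 1: not given; f = 1 as the extreme, f = 0.5 as an illustration.
- CEA-silent metastases have the same site mix as the rest, and a silent lung metastasis at year 1 is not seen.

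**Reading A: year-1 scans are pooled with later ones**

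Apparent miss rate = m(1 − fL) / [(1 − m) + m(1 − fL)].

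With f = 1, per 100 recurrences:
- m = 0.20: 20 silent, 6 in the lung and unseen; 14/94 = 14.9%.
- m = 0.40: 40 silent, 12 unseen; 28/88 = 31.8%.
- m = 0.60: 60 silent, 18 unseen; 42/82 = 51.2%.

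With f = 0.5 and m = 0.40: 0.40 × 0.85 = 0.34; 0.34/0.94 = 36.2%.

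Sensitivity of the f = 1 result to the inputs: for L from 0.20 to 0.40 and m from 0.20 to 0.60, the understatement runs from about 3 to 13 percentage points (5 to 9 at L = 0.30). If CEA is less sensitive in the lung (assumed 0.5 against 0.7 elsewhere), the true miss rate is 0.30 × 0.5 + 0.70 × 0.3 = 36%. The apparent rate is 0.21/(0.64 + 0.21) = 24.7%, a wider gap than under an equal site mix.

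**Reading B: only scans that cover thorax and abdomen count**

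Taken literally, the year-1 abdominal CT is not the scan that 8.1.2 names. A CEA-silent liver metastasis found on it then drops out of the numerator, while a metastasis found in the same period on a CEA-triggered thorax/abdomen CT still counts as flagged. As an illustration, take m = 0.40, f = 0.5, and assume that none of the dropped cases is counted later. Then 0.40 × 0.5 = 0.20 remain silent and the rate reads 0.20/(0.60 + 0.20) = 25%. The field mismatch is gone, but the miss rate is again too low unless the flagged cases of that period are dropped as well, which the protocol does not say.

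**The case against.** The strongest reply is that 8.1.2 already names a thorax/abdomen scan, so a literal reader would use only the later scans, and that tabulation by site and time belongs in a SAP. The first part is a possible reading, but Reading B shows that it trades one loss for another. The second would be right if detail were merely missing. Here the protocol itself fixes both the reference scan and the schedule, and the two do not agree.

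Other parts of the reply stand and limit the point:

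- A reader might infer that every CEA-versus-CT comparison is affected. It is not. Endpoint 4.2(3), "The correlation between CEA and helical CT abdomen/thorax", goes on to ask whether disease can be localised when CEA points to it. That question, like the 8.1.2 parameter on CT findings after a CEA rise, concerns only CEA-positive patients, who are to have the full field.
- A reader might infer a biased verdict on replacing imaging by CEA. No section sets that aim: the objective uses both tools, and 2.2 says imaging is advised because CEA misses recurrences.
- A reader might take the f = 1 figures as the expected bias. Patients may enter up to three years after treatment, and those past year 1 when they start the new schedule never have the abdomen-only scan, so the pooled effect is smaller.
- It would be too strong to say that silent lung metastases cannot be seen. An abdominal CT may show the lung bases, lung disease may coexist with abdominal disease, and the year-2 scan covers the chest.
- A rule that a later lung lesion must not count as CEA-detected because the year-1 scan could not show it is unworkable. Without chest imaging at year 1, nobody can tell whether the lesion was there.

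**Conclusion.** The point holds for the false-negative rate in 8.1.2, and for the ROC work so far as it uses routine CT as the reference. The named reference does not match the year-1 scan, and under either reading the miss rate tends to be understated. The mismatch and its direction follow from the text; the size does not. Under the assumptions above, true miss rates of 20%, 40% and 60% would read 15%, 32% and 51% if all recurrences were judged at year 1, which is the extreme for an equal site mix. With half judged at year 1, 40% would read about 36%. The 30% covers all lung first recurrences, not lung-only silent ones, which makes these figures a ceiling in that respect; lower CEA sensitivity in the lung would work the other way. The sample size does not depend on this point.

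**What to change.** Amend 8.1.2 so that the comparison follows the imaging field:

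- At year 1, compute the false-negative rate and the ROC reference for abdominal sites only, in CEA-positive and CEA-negative patients alike. A lung finding on a CEA-triggered CT does not enter the year-1 figure.
- Compute the thorax/abdomen version only at scheduled CTs that image the chest.
- Report lung separately, and state as a limitation that lung lesions silent at year 1 cannot be verified.

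This is a change of wording and one site-specific table. It asks for no extra scan, leaves the imaging schedule as it is, and needs no change to 4.2(3). The cost is that fewer patients contribute to the lung estimate, so it is less precise.
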